#### Baseline characteristics

Patient demographics and baseline disease characteristics will be summarized using descriptive statistics. These characteristics include age, sex, tumor location, histological subtype and tumor differentiation grade, TNM stage, baseline tumor burden, PD-L1 expression status, mismatch repair (MMR) status, and prior treatments. Continuous variables will be reported as the mean and standard deviation (SD) if the data are approximately normally distributed, or as the median and interquartile range (IQR) if the distribution is skewed. Categorical variables will be summarized as counts and percentages.

#### Efficacy endpoints

This is a single-arm exploratory trial; therefore, all efficacy results will be descriptive with no formal between-group comparisons. The primary efficacy endpoint for Phase II is the ORR, defined as the proportion of patients achieving a best overall response of CR or PR as determined by investigator assessment according to RECIST v1.1. The first tumor assessment is scheduled at approximately 6 weeks of therapy, which corresponds to the end of two treatment cycles. ORR will be reported along with a two-sided 95% exact confidence interval calculated using the Clopper–Pearson method. In the ITT analysis, patients with no post-baseline tumor assessments will be considered non-responders for the purpose of calculating ORR. The observed ORR will be compared qualitatively to historical outcomes from first-line therapy for advanced GC/GEJC; however, no formal hypothesis testing will be performed due to the single-arm study design.

Secondary efficacy endpoints will be analyzed and reported descriptively. PFS is defined as the time from treatment initiation until radiologic disease progression or death. It will be estimated using the Kaplan-Meier method; the median PFS and its two-sided 95% confidence interval will be reported. Patients who are alive without progression at the time of analysis will be censored at the date of their last disease assessment. DCR is the percentage of patients achieving CR or PR or sustained stable disease for at least 6 weeks. DCR will be reported with a two-sided 95% exact confidence interval calculated by the Clopper-Pearson method. For the subset of patients who undergo curative-intent surgery (R0 resection) after successful therapy, a 2-year DFS rate will be calculated. This rate will be defined as the proportion of those post-surgery patients who are alive and recurrence-free 24 months after surgery. Because this subset is expected to be small, the 2-year DFS will be presented as a descriptive metric without formal statistical comparison. OS is defined as the time from treatment initiation until death from any cause. The 24-month OS rate will be estimated using Kaplan-Meier methods, and if sufficient follow-up is available, the median OS and its 95% confidence interval will also be reported. If the median OS is not reached by the analysis time, the survival rate at the last follow-up time point will be provided instead. Patients who are alive at the time of analysis (or last known follow-up) will be censored on that date for OS and DFS analyses. Patient-reported quality of life outcomes will be summarized at baseline and at specified time points during treatment. Changes from baseline in QoL scores may be explored with paired statistical tests, depending on data distribution, as an exploratory analysis.

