## Methods

This is a prospective, single-center, single-arm phase Ib/II clinical trial designed to evaluate the efficacy and safety of XELOX in combination with sintilimab and HBOT in HER2-negative advanced or metastatic GC/GEJC patients. The study protocol and informed consent forms were reviewed and approved by the Academic Review Committee and Ethics Committee of West China Hospital, Sichuan University (WCH20242269). The clinical trial will be conducted in accordance with the Declaration of Helsinki and good clinical practice guidelines. All the participants provided written informed consent, and all the data were kept confidential. No independent committees were established for this single-arm clinical trial. The clinical trial is prospectively registered on ClinicalTrials.gov (NCT06742411).

Phase Ib uses a standard 3 + 3 dose−escalation design to evaluate the safety/tolerability of XELOX plus sintilimab with HBOT and to identify the recommended Phase II HBOT regimen (RP2D). Approximately nine patients are expected in Phase Ib per the 3 + 3 algorithm (no formal power calculation), and Phase Ib enrollment does not contribute to the Phase II power determination.

For Phase II, the sample size is based on the primary endpoint of ORR. Historical first−line data for XELOX plus PD−1 inhibitors suggest an ORR of 58%. Assuming the addition of HBOT increases ORR to 73%, a two−sided α=0.20 and 80% power in an exact single−arm binomial framework yield a required sample size of 45 patients. Allowing for 5% attrition, the planned Phase II enrollment is 48 patients. This calculation is signal−seeking and estimation−oriented rather than confirmatory. Detailed statistical methods are described in the Statistical Analysis section.

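### Phase II is sized by α and power, but the plan performs no test: the stated 80% power attaches to no analysis, and no signal threshold or precision target is stated

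*Protocol article*

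**What the plan says.** **Sizing (Methods, sample-size paragraph).** The historical ORR is taken as 58% and the ORR with HBOT as 73%. The article states that "a two−sided α=0.20 and 80% power in an exact single−arm binomial framework yield a required sample size of 45 patients". It continues: "Allowing for 5% attrition, the planned Phase II enrollment is 48 patients". It then qualifies the exercise: "This calculation is signal−seeking and estimation−oriented rather than confirmatory".

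**Analysis (Statistical analysis, Efficacy endpoints).** For the primary endpoint, "ORR will be reported along with a two-sided 95% exact confidence interval", by Clopper–Pearson. The result is set against historical outcomes qualitatively, and "no formal hypothesis testing will be performed due to the single-arm study design".

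**Population and missing responses (Analysis populations; Efficacy endpoints; Missing data).** The primary set is the Phase II ITT population, meaning all treated patients. Those without a post-baseline tumour assessment stay in the denominator as non-responders.

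**The concern.** Type I error and power describe a decision rule: how often it declares a signal when the true rate is 58%, and how often when it is 73%. The Methods section quotes both. The efficacy section then declines to apply any rule and reports an interval at a different level: 95% corresponds to two-sided α=0.05, not 0.20. The stated reason, that the trial has a single arm, does not explain the gap, because the sizing calculation is itself a single-arm comparison with a fixed rate.

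The purpose label does not settle it either. A signal-seeking design needs a definition of a signal, and an estimation design needs a target precision. The article states neither, and α with power is the only justification offered for 48 patients.

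At stake is how the primary result will be read. The Discussion expects the trial to lay the ground for randomised trials, so someone will have to judge whether the result is good enough. ORR is investigator-assessed and the article says that no independent committees were set up, so a number fixed in advance is a main protection against interpretation after the fact.

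**Working it through.** **Inputs.** From Methods: p0 = 0.58, p1 = 0.73, two-sided α = 0.20 (upper tail 0.10), power 0.80, attrition 5%. From Efficacy endpoints: two-sided 95% Clopper–Pearson interval, no test.

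**1. Reproduce the plan's own figure.** Normal approximation for one proportion:

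n = [(z0.90·√(p0·q0) + z0.80·√(p1·q1)) / (p1 − p0)]²
= [(1.2816·√(0.58·0.42) + 0.8416·√(0.73·0.27)) / 0.15]²
= [(0.6325 + 0.3737) / 0.15]² = 44.99, so 45.

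Attrition: 45 / 0.95 = 47.4, so 48. Both figures reproduce.

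Exact binomial check with upper tail at most 0.10:
- n=45: at least 31 responders, type I error 9.05%, power 78.8%.
- n=48: at least 33 responders, type I error 8.5%, power 79.8%.

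A strict exact search first reaches 80% at n=50. So 45 is the normal-approximation answer under an exact label, short by about one point of power.

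**2. The rule that matches the sizing (n=48).** Two-sided α=0.20 corresponds to an 80% interval. Its Clopper–Pearson lower limit is 56.5% at 32/48 and 58.6% at 33/48, so 33 is the first count that excludes 58%.
- P(X ≥ 33 | 0.58) = 0.0850
- P(X ≥ 33 | 0.73) = 0.7978

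**3. The reported 95% interval, if it were required to exclude 58% (hypothetical).** Its lower limit is 55.9% at 34/48 and 58.2% at 35/48, so 35 is the first qualifying count.
- P(X ≥ 35 | 0.58) = 0.0238
- P(X ≥ 35 | 0.73) = 0.5791

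At n=45 the corresponding count is 33, with power 55.7%.

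**4. Where the two readings disagree.** They part at 33 or 34 responders. The probability of landing there is 0.7978 − 0.5791 = 0.219 if the true ORR is 73%, and 0.0850 − 0.0238 = 0.061 if it is 58%.

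**5. Effect of unassessed patients.** Assume that 73% applies only to assessed patients and that 5% of the 48 are unassessed. The ITT ORR is then 0.73 × 0.95 = 0.6935. Power becomes 60.5% for the 33-of-48 rule and 35.9% for the 35-of-48 rule. The 79.8% therefore requires 73% to be the ITT rate, with unassessed patients already counted as failures.

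**6. Precision at n=48.** The 95% interval runs from 53.8% to 81.3% at 33/48, from 55.9% to 83.1% at 34/48 and from 58.2% to 84.7% at 35/48. Widths are about 27 to 28 points, so the average half-width is about 13 to 14 points. The intervals are not symmetric about the estimate.

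**The case against.** The protocol is open about what it is doing. It calls the calculation non-confirmatory and the trial exploratory, and the Discussion lists the small sample and the missing control group as limitations. Using a lenient α to choose a sample size and then reporting a conventional 95% interval is common and can be coherent. The article will give an estimate and interval beside a stated 58% benchmark and 73% target, so readers can apply a rule of their own. It also condenses a full protocol (Version 1.3) that is not shown.

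Much of this stands, and it rules out four stronger readings that a reader might infer:

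- *The trial has only 58% power.* That figure belongs to a rule under which the 95% lower limit must exceed 58%. The article never adopts that rule.
- *Any observed ORR above 58% will be called promising.* With no HBOT effect, 28 or more of 48 would occur 54.3% of the time, but the article does not say that it would call this a signal. At 28/48 its own interval would be 43.2% to 72.4%, which shows none.
- *The sample size is miscalculated.* It reproduces.
- *No threshold exists anywhere.* Only its absence from this article can be asserted.

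What does not stand is that the matter is detail left to a fuller document. The article expressly excludes a test and makes the comparison qualitative, so an analysis plan that added the matching test would contradict it. Nor does the non-confirmatory label supply the missing definition: it explains a lenient α, not a power figure for a rule that is then set aside.

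**Conclusion.** The point holds as an internal inconsistency. The sole justification for 48 patients is the power of a procedure that the efficacy section says will not be carried out, and the article states no signal threshold or precision target in its place. The practical size is the band of 33 to 34 responders (68.8% to 70.8%): a signal under the sizing rule, but with 58% still inside the reported 95% interval. A truly 73% regimen would land there about 22% of the time. These figures assume 48 treated patients and independent responses, with 58% and 73% as ITT rates. The 57.9% is a what-if, not a property of the plan. This is a should-fix, not a fatal defect: endpoint, population, estimator and enrolment are unaffected, and the trial claims no confirmatory status.

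**What to change.** Choose one of two wordings.

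**(a) Keep the power statement and give it a rule.** For example: *HBOT will be considered worth further study if at least 33 of 48 Phase II ITT patients respond, that is, if the lower limit of the two-sided 80% Clopper–Pearson interval exceeds 58%. The exact one-sided type I error is 8.5% and power is 79.8% if the ITT ORR, with unassessed patients counted as non-responders, is 73%. Power is about 60% if 73% applies only to assessed patients and 5% are unassessed.* Report the 80% interval beside the 95% interval, and amend the no-testing sentence to fit. If the ITT number differs from 48, recompute the threshold. Recruitment began on 31 December 2024, so fix this before Phase II response data are reviewed.

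**(b) Make it an estimation study.** Delete the α and power statement and justify 48 patients by the expected 95% interval, about ±13 to 14 points near an ORR of 70%.

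Either way the cost is wording in two sections and no extra patients. Under (a) the sponsor commits to a visible threshold. Under (b) it gives up the power claim.

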##### Missing data

For the primary endpoint ORR in the ITT population, patients who have no post-baseline tumor assessments will be counted as non-responders. For time-to-event endpoints such as PFS, DFS, or OS, patients who have not experienced the event by the cutoff date will be censored at the time of their last adequate disease assessment. If scheduled visits or assessments are missed, all data collected up to the point of patient withdrawal or loss to follow-up will be included in the analysis, and no forward imputation of missing future observations will be performed. Missing data in patient-reported outcome measures, such as QoL questionnaires, will not be imputed; analyses will be based on available data only.

To address the potential impact of missing data, we may conduct additional exploratory analyses using methods that accommodate data missing at random. For example, a linear mixed-effects model for repeated measures could be employed to explore longitudinal trends in QoL scores despite some missing follow-up data. If more than 10% of patients have missing data for the primary endpoint, we will perform additional sensitivity analyses to ensure the robustness of our conclusions. These may include using multiple imputation techniques to estimate missing outcomes and conducting best-case and worst-case scenario analyses to gauge the potential range of impact due to the missing data.

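### Two-year DFS is defined as a simple proportion at 24 months but also censored, with two different censoring dates; the proportion is biased downward if any resected patient is event-free with under 24 months of follow-up

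*Protocol article*

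**What the plan says.** All three statements are in the protocol article, under Statistical analysis.

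- **Definition (Efficacy endpoints).** For patients with an R0 resection, the two-year DFS rate is "the proportion of those post-surgery patients who are alive and recurrence-free 24 months after surgery".
- **First censoring rule (Efficacy endpoints, same paragraph).** "Patients who are alive at the time of analysis (or last known follow-up) will be censored on that date for OS and DFS analyses".
- **Second censoring rule (Missing data).** "For time-to-event endpoints such as PFS, DFS, or OS, patients who have not experienced the event by the cutoff date will be censored", and the date given there is different: they are "censored at the time of their last adequate disease assessment".

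For the parallel overall survival endpoint the estimator is named: "The 24-month OS rate will be estimated using Kaplan-Meier methods". Kaplan-Meier is also named for PFS, but not for DFS. The DFS result is to be descriptive: "Because this subset is expected to be small, the 2-year DFS will be presented as a descriptive metric without formal statistical comparison". The article gives no DFS analysis date and no minimum follow-up after surgery.

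**The concern.** A simple proportion needs a yes or no for every patient in the denominator. A patient who is recurrence-free at 15 months when the data are cut is neither, and the definition has no place for that patient. The censoring rules do provide for such patients, but they belong to a different estimator.

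Short follow-up is a realistic prospect. DFS runs from surgery, surgery comes some time after enrolment, and recruitment is spread over two years. An analysis timed for two-year OS could therefore catch the later resections before 24 months. Loss to follow-up has the same effect at any cut.

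The Discussion says that this endpoint is there to show how lasting disease control is after conversion surgery. A rate that depends on an unstated choice about incomplete patients serves that purpose poorly. With few patients, the choice could also be made after the data are seen.

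**Working it through.** The article states no DFS figure to reproduce, so the check has two parts.

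**1. The texts side by side**

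| Place | DFS treated as | Patient event-free before 24 months |
|---|---|---|
| Efficacy endpoints, definition | yes/no proportion | no rule |
| Efficacy endpoints, later sentence | censored | censored at analysis or last known follow-up, if alive |
| Missing data | censored time-to-event | censored at last adequate disease assessment |

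The definition conflicts with both censoring rules, and the two rules conflict on the date. Read literally, the Efficacy endpoints rule censors for DFS anyone who is alive, without requiring that they be recurrence-free. The rule that counts unassessed patients as non-responders is written for ORR only.

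**2. Size, under stated assumptions**

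From the article (Trial registration details): recruitment from 31 December 2024 to about 31 December 2026, 24 months.

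Assumed: uniform accrual; cut 24 months after last enrolment; surgery L = 4 or 6 months after enrolment (six 21-day cycles take about 4 months); exponential DFS with true 24-month rate S = 40, 50 or 60%; censoring unrelated to prognosis.

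Potential follow-up after surgery is then uniform between 24 − L and 48 − L months.

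- Share with under 24 months of potential follow-up: L/24 = 4/24 = 16.7% to 6/24 = 25%.
- Share undetermined (short follow-up and still event-free at the cut): U = S × (S^(−L/24) − 1) / (−ln S).

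| S | U, L = 4 | U, L = 6 |
|---|---|---|
| 40% | 7.2% | 11.2% |
| 50% | 8.8% | 13.6% |
| 60% | 10.4% | 16.0% |

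At S = 50%:

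- Counted as failures, S × (1 − L/24): 0.5 × 0.833 = 41.7% (L = 4); 0.5 × 0.75 = 37.5% (L = 6).
- Left out, S × (1 − L/24) / (1 − U): 0.417/0.912 = 45.7% (L = 4); 0.375/0.864 = 43.4% (L = 6).
- Kaplan-Meier at 24 months: 50% in both cases.

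Both versions of the proportion fall short for the same reason. Every early recurrence is counted, while an event-free patient who has not reached 24 months cannot count as a success.

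The result depends on the cut. With S = 50% and surgeries uniform over 24 months, simulation gave:

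| Cut after last surgery | As failures | Left out | Kaplan-Meier |
|---|---|---|---|
| 6 months | 12.5% | 25% | 50% |
| 12 months | 25% | 36% | 50% |
| 18 months | 37.5% | 43% | 50% |
| 24 months | 50% | 50% | 50% |

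The 18-month row is the L = 6 case above.

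**Invented example of eight resected patients.** Recurrences at 6 and 14 months; recurrence-free and censored at 8, 12 and 18 months; three recurrence-free at 24 months. Counted as failures: 3/8 = 37.5%. Left out: 3/5 = 60%. Kaplan-Meier: 7/8 × 4/5 = 70%. One data set yields three rates, and the article does not settle which is meant.

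**The case against.** The strongest reply is that the proportion merely names the quantity, the probability of being alive and recurrence-free at 24 months, and that the censoring rules imply Kaplan-Meier. What remains is then an unnamed estimator, which an article may leave to the SAP. Part of this stands. A reader might infer that the plan counts recently resected patients as failures or drops them. No sentence says either, and the only written instruction for incomplete DFS follow-up is to censor. But the same section names Kaplan-Meier for PFS and for 24-month OS and gives DFS a proportion instead. That, together with two unlike censoring dates, is a conflict in the stated text and not just detail left out.

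The second reply concerns size, and most of it stands.

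- A cut at about the end of December 2028 (24 months after last enrolment) and the surgery lag are assumptions. If DFS is reported once every resected patient has been followed for 24 months, nothing is biased.
- A reader might take the 17 to 25% with short potential follow-up as the share misclassified. It is not, because those who recurred or died before the cut are already determined. The undetermined share is 7 to 16%, or about 0.6 to 1.3 of an assumed eight patients.
- The Intervention section allows surgery during therapy. With surgery at 1.5 to 3 months, only 1.5/24 = 6% to 3/24 = 12.5% would have short follow-up. Later surgery would raise the share.
- With eight patients and a rate of 50%, the standard error is √(0.25/8), about 18 points, which is larger than either bias in the main scenario.

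Imprecision does not excuse an undefined estimator, though. A descriptive rate still needs one definition, fixed before the data are seen.

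**Conclusion.** The point holds as a conflict in the text with a conditional consequence. The stated proportion does not fit the stated censoring, and the two censoring rules disagree. The proportion is biased downward if, and only if, some resected patient is event-free with under 24 months of post-surgery follow-up at analysis, through late surgery or loss to follow-up.

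Under the assumed cut, the shortfall at a true rate of 50% is about 8 to 12.5 points if such patients count as failures and about 4 to 7 points if they are left out. An earlier cut makes it larger. The documents do not support the firmer statement that the reported rate will be wrong, because they fix neither the DFS cut-off nor the timing of surgery.

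The endpoint is secondary, descriptive and confined to a small subset. The ORR primary analysis is untouched. The text should be corrected, but this is not a threat to the trial's main result.

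**What to change.** In Efficacy endpoints, replace the proportion with the Kaplan-Meier estimate of DFS at 24 months from the date of R0 resection, with its 95% CI and the number at risk at 24 months. State that the event is recurrence or death, and that patients alive and recurrence-free are censored at their last adequate disease assessment.

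Then reconcile the Efficacy endpoints censoring sentence with Missing data, so that DFS has one date and being alive after a recurrence is not grounds for censoring.

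If the sponsor prefers a proportion, it can be kept for patients with at least 24 months of potential follow-up after surgery, provided a rule for losses to follow-up is added. Kaplan-Meier is simpler and matches the handling of 24-month OS.

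The cost is a sentence or two of text. No new data are needed.

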## Trial registration details

The clinical trial is registered at ClinicalTrials.gov (Identifier: NCT06742411) and conforms to the World Health Organization Trial Registration Data Set. The schedule of enrolment, interventions, and assessments is illustrated in **Figure 1**. This study is conducted in accordance with Protocol Version 1.3, dated 31 October 2024. Participant recruitment began on 31 December 2024 and is expected to be completed by approximately 31 December 2026.

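### When median OS is not reached, the plan substitutes survival at a data-driven last follow-up time, a figure shown only when the curve stays above 50% and so too high on average (minor)

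*Protocol article*

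**What the plan says.** Two-year OS is a secondary endpoint (Endpoints section). Under Efficacy endpoints the article states: "The 24-month OS rate will be estimated using Kaplan-Meier methods". It adds that the median OS and its 95% confidence interval will be given if follow-up is sufficient. Then comes the fallback: "If the median OS is not reached by the analysis time", "the survival rate at the last follow-up time point will be provided instead".

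The last follow-up time point is not defined further, and no calendar date or minimum follow-up is given for the OS analysis. On censoring, the same section says: "Patients who are alive at the time of analysis (or last known follow-up) will be censored on that date for OS and DFS analyses". The Missing data section instead names the last adequate disease assessment for time-to-event endpoints including OS, which leaves the end of the OS curve less certain still.

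Entry is staggered: "Participant recruitment began on 31 December 2024 and is expected to be completed by approximately 31 December 2026". On size: "Allowing for 5% attrition, the planned Phase II enrollment is 48 patients".

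**The concern.** Three features of the rule combine.

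- **The time point is whatever the data produce.** Survival at last follow-up belongs to the longest-followed patient, not to a month chosen in advance. It cannot be set beside a landmark rate from another study.
- **Follow-up there is thin.** With staggered entry, few patients are observed near the end of the curve.
- **Display depends on the result.** The median is unreached only if the curve stays above 50% to its end. The substitute is therefore printed when it is above 50% and withheld otherwise.

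A figure shown only when it is high is biased upward, even if the estimator itself is sound. At stake is one descriptive number, placed where readers expect the median, that makes late survival look better than it is.

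**Working it through.** **The plan's own figure.** The article gives no figure for OS precision. The only number to reproduce is the sample size. With ORR 58% versus 73%, two-sided α = 0.20 and 80% power:

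n = [(1.2816·√(0.58·0.42) + 0.8416·√(0.73·0.27)) / 0.15]² = [(0.6325 + 0.3737) / 0.15]² = 44.99, so 45.

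Then 45/0.95 = 47.4, so 48. This agrees with the article, and 48 is used below.

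**Inputs from the article.** 48 patients; recruitment window of about 24 months; the fallback rule and its trigger; censoring at the analysis date.

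**Assumptions not in the article.** Uniform entry over months 0 to 24; exponential OS, S(t) = 2^(−t/m), with true median m; no loss to follow-up; data cut at month 30, 36 or 48 (6, 12 or 24 months after the last enrolment). The Kaplan-Meier estimate is Ŝ(t) = Π(1 − dᵢ/nᵢ), and the fallback is triggered when Ŝ at the largest observed time exceeds 0.5.

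**A bound without simulation.** Any displayed figure exceeds 50%. At m = 24 and cut 30, the longest follow-up is about 29 months, where true survival averages 0.432. The mean excess must then be more than 50 − 43.2 = 6.8 points. At cut 36 the true value is 0.364, and the bound is 13.6 points.

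**Simulated means over the trials in which the fallback is shown** (6,000 runs per row):

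| True median | Cut (month) | Fallback triggered | Reported | True | Excess (points) |
|---|---|---|---|---|---|
| 30 | 30 | 58% | 0.599 | 0.510 | 8.9 |
| 30 | 36 | 36% | 0.570 | 0.445 | 12.5 |
| 24 | 30 | 34% | 0.570 | 0.432 | 13.8 |
| 24 | 36 | 12% | 0.548 | 0.364 | 18.4 |
| 18 | 30 | 8% | 0.546 | 0.328 | 21.8 |
| 18 | 36 | 1% | 0.528 | 0.263 | 26.5 |

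Repeat runs differ by about one point in trigger frequency and by less in excess, except in the last row, where few trials trigger.

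**Source of the bias.** Computed in every trial, the tail value is practically unbiased: 0.433 versus 0.434 at m = 24, cut 30, and 0.330 versus 0.333 at m = 18, cut 30. The conditional display creates the excess.

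**The 24-month rate.** Over all trials it is unbiased (0.499 versus 0.500 at m = 24, cut 30). Within the triggered trials it is also high: +8.0 and +8.9 points at m = 24 (cuts 30 and 36), and +4.4 and +4.7 at m = 30.

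**Numbers at risk when triggered.** About 2 patients are still followed in the last month. The Kaplan-Meier value is fixed earlier, at the last death, with about 12 to 15 at risk.

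**Later analysis.** At cut 48 the fallback is triggered in 0% of trials at m = 18, 0.4% at m = 24 and 5.7% at m = 30.

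**Sensitivity.** With entry over months 6 to 24 (leaving time for Phase Ib) and m = 30, the cut-30 figures are 0.633 versus 0.582, an excess of 5.1 points triggered in 78% of trials; at cut 48 the trigger rate is 13%. With entry over months 0 to 24 and 1% loss per month, it is 8.7% at m = 30, cut 48.

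**The case against.** The strongest reply is that little depends on this number. All efficacy results are descriptive, no decision uses the fallback, and the 24-month rate, which is the named OS endpoint, is reported in every case. The fallback replaces only a median that cannot be estimated. All of this stands, and it is why the point is minor. It does not justify the rule: an always-reported 24-month rate makes the fallback unnecessary but does not correct it.

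A second reply is that the excess is partly generic, because any survival estimate runs high in trials with few deaths. This also stands. Setting the tail's bias in triggered trials against the 24-month rate's bias in all trials would be unequal. Like for like, the excess specific to the tail is about 8.9 − 4.4 = 4.5 to 13.8 − 8.0 = 5.8 points at cut 30, and 12.5 − 4.7 = 7.8 to 18.4 − 8.9 = 9.5 at cut 36.

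A reader might infer more than the article supports:

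- *That the estimate rests on two patients.* Two is the number still followed in the last month. The estimate is set at the last death, with far more at risk.
- *That survival will be overstated by 22 to 27 points.* Those gaps arise at a true median of 18 months, where the fallback appears in about 8% and 1% of trials.
- *That OS will be judged against historical outcomes.* The article states its qualitative historical comparison for ORR only.

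The last follow-up time point could also mean a scheduled visit, but the text does not say so. An interval or number at risk for this figure may be given in the full protocol or SAP, so their absence here is not held against the article.

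**Conclusion.** The point holds as a minor reporting defect. Followed as written, the rule yields a figure tied to no fixed month and displayed only when it exceeds 50%. That it is selected to be high follows from the definition of an unreached median and needs no simulation.

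The size does rest on assumptions: exponential OS, uniform entry over 24 months and the analysis date. For analysis 6 to 12 months after the last enrolment, the average excess is about 9 to 12 points at a true median of 30 months (shown in 58% and about 36 to 37% of trials) and 14 to 19 points at 24 months (34% and about 12 to 13%). It is larger where the fallback is rarer. With analysis 24 months after the last enrolment, the fallback appears in about 5% of trials or fewer, rising to 13% if entry starts at month 6 and the true median is 30 months. The planned two-year OS endpoint is not undermined.

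**What to change.** Delete the fallback sentence. When the median is not reached, say so and give its lower 95% confidence limit. Rely on the 24-month Kaplan-Meier OS rate already planned, optionally with a 12-month rate, each with a 95% confidence interval and the number at risk, and report these whether or not the median is reached. The unconditional reporting is what removes the selection.

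The cost is one sentence in the analysis section. No patients, data or changes to the primary analysis are needed.
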